### Intervention design

#### Enrollment procedures

Families of eligible preterm neonates will be approached for participation and consent when their child is close to moving from the NICU to the step-down unit, called the Packard Intermediate Care Nursery (PICN), indicating that they are medically stable. This procedure also ensures that the auditory capacities of neonates are adequately developed to perceive speech [39]. Moreover, the PICN is generally a quieter environment suitable for playing voice recordings.

#### Speech recording procedures

Language samples will be obtained from each mother as she reads a chapter from a children’s storybook that is available in English and in Spanish. Speech recording will be obtained prior to randomization to mask parents and research staff to group assignment. We will counsel all mothers to imagine reading to the infant. Recordings will be approximately 30 min and normalized for intensity and segmented using an auditory software (Praat: http://www.fon.hum.uva.nl/praat/) [40].

#### Randomization and RCT design elements

Eligible participants will be randomized by the principal investigator ([name]), who will not be blinded, in order to provide close monitoring of the procedures. The principal investigator will allocate participants sequentially as they are enrolled to either the T or the C group using the minimization algorithm by Pocock and Simon [41] implemented in the R statistical software package [42]. Randomization will be stratified for (1) GA (24-0/7 to 27-6/7 weeks or 28-0/7 to 31-6/7 weeks), to control for potential development differences in response to the intervention and as a proxy for neural injury, and (2) socioeconomic status (SES) (above versus below average SES; based on Hollingshead Index (HI) [36, 43]), to control for potential differences in language outcomes affected by socioeconomic factors. Taking into account ethical considerations and parental preferences, twins and multiples will be assigned to the same group [44]. Families and research and clinical staff will be blinded to the group status. In the unlikely event that a family, research staff, or clinical staff suspect that an infant may not tolerate the speech recording, the principal investigator will reveal the group assignment.

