## Methods

### Study design

To achieve these aims, we propose an RCT that will involve 42 very preterm infants born and cared for at Stanford’s Lucile Packard Children’s Hospital (LPCH). Enrollment is planned from November 2019 to December 2021. For infants who meet the inclusion criteria of gestational age at birth (GA) of 24-0/7 to 31-6/7 weeks, we will obtain informed consent and questionnaires about the family’s demographics and language from parents, and a speech recording from each mother. Infants will then be randomized to the treatment (T) or control (C) group. Infants randomized to either T or C group will receive standard medical care, with the exception that infants randomized to the T group will also receive the maternal speech intervention achieved by playing recordings of maternal voice via iPods placed in an infant’s incubator or open crib. Infants in the C group will have the same auditory setup to ensure that parents and clinical staff remain blinded to the group status. The duration of the intervention will begin once an infant gets transferred to the intermediate care nursery, indicating medical stability, and end once an infant has received their clinical MRI, which is part of the standard medical care at LPCH and is performed prior to hospital discharge (~ 36–38 weeks PMA). The long-term effects of the intervention will be assessed at 12 months and 18 months AA. At 12 months AA, infant participants will undergo a dMRI scan during natural sleep, and parents will complete the MacArthur-Bates Communicative Development Inventories (CDI): Words and Gestures Questionnaire [37]. At 18 months AA, parents will complete another CDI: Words and Gestures Questionnaire, the primary outcome assessment of language development (see Fig. 1).

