#### Delivery of intervention

The intervention will occur for a minimum of 2 weeks (28 h) and a maximum of 9 weeks (126 h) prior to the date of the clinical brain imaging scan. Neonates randomized to the T group (maternal speech group) will listen, via an iPod placed in cribs and/or incubators, to recordings of their mother’s speech at hourly intervals between 10:00 p.m. and 6:00 a.m. Administration of the intervention during periods when parents are unlikely to visit the hospital is expected to minimize parental knowledge for the group assignment. Recordings will be played automatically using the alarm function to avoid reliance on clinical staff. Research staff will regularly check on the status of the device to ensure proper functioning. Neonates will hear a total of 2.67 h of speech recordings per night (20 min/h × 8 h). Treatment length will be defined as the number of nights from the start of treatment (i.e., beginning of PICN stay) to the end of treatment (i.e., date of MRI scan at 36–38 weeks PMA). Within a given hour, two 10-min segments will be randomly presented to avoid synchronization with biological and sleep rhythms. Sound intensity for speech recordings is balanced between open cribs versus incubators and is below hourly NICU safety levels less than 50 dB [45].

Neonates in the C group will receive standard care. All infants in the NICU receive developmental care support from health care providers and families, and clinical staff tracks which activities are experienced by all infants through nursing documentation. Clinical staff uses a standard care path to guide which types of activities are appropriate for an infant depending on the maturity and health status. Families are generally encouraged to talk, read, and sing to their infants when visiting, if the infant is deemed in the appropriate stage. Auditory setup will be the same for neonates in the C group; however, these neonates will not hear speech recordings. This procedure ensures that parents remain blinded to the group randomization.

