#### Control variables and covariates

To characterize the sample and ensure balance across groups in analyses for treatment effects, we will prospectively collect the following information from electronic medical records and parent report questionnaires to control for (1) major medical complications associated with prematurity, including GA, birth weight, sex, history of antenatal steroid usage, infection, number of days of intubation and oxygen, and X-ray changes consistent with chronic lung disease; (2) PMA at MRI scan; (3) the number of nights of exposure to study treatment; and (4) sociodemographic factors associated with later language outcomes, including the SES of primary caretakers as measured by the HI [43], the frequency and number of languages spoken by adult and child household members, and number of siblings.

We will also obtain metrics to ensure balance across groups on the basis of the amount of language exposure experienced by infants in their home environments. To collect data on naturalistic maternal/caregiver input during the infancy period, we plan to use the Language ENvironment Analysis (LENA) recording device and software [54]. Families will be asked to perform two full-day (16 h) home LENA voice-recording sessions immediately around the time of the 12 months AA visit for MRI scanning. From this device, we will examine the adult words count measure per hour, normalizing for the length of audio recording, since it is the most accurate measure from LENA at this age when the infants may have limited language production skills [55]. If the groups do not match, we will use this language exposure metric as a covariate in the analyses.

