### Analysis plan

#### Power calculations

We calculated the sample size based on power. The significance level is *p* < 0.05 for all analyses. Power estimates are based on the means, standard deviations, and samples size from an RCT neuroimaging study of preterm neonates that showed a significant effect of a parent-based NICU intervention on diffusion metrics measured at close-to-term age (Cohen’s *d* = 1.03) and developmental outcomes (Cohen’s *d* = 1.77) measured at 9 months AA [56]. Thus, if we assume an effect size that is more conservative than this earlier study, specifically Cohen’s *d* = 1.0, we will have a power of ß = 0.8, if we enroll a sample size of at least 17 participants per group. Therefore, our planned enrollment of 21 participants per group will yield a power of ß = 0.88 to detect an effect size at that level (Cohen’s *d* = 1.0). If our effect size is even smaller than we anticipate, for example, Cohen’s *d* = 0.9, a planned enrollment of 21 per group will still yield a power greater than 0.8 to detect a treatment effect.

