#### Analytic strategy

We anticipate that stratification prior to randomization will result in a close matching of T and C groups on demographic and health variables. Prior to statistical analyses, we will use independent samples t-tests (continuous variables) or chi-square tests (categorical variables) to assess the statistical balance between T and C groups on the basis of GA, sex, SES, clinical complications associated with premature birth, and language exposure during treatment and after hospital discharge. Analyses will use an intention-to-treat strategy [57]. If groups are matched on all variables, we will use independent t-tests (two-tailed) to compare T versus C groups on the primary long-term language outcome and the secondary short-term outcomes that relate to white matter development. Should groups not be balanced, and to account for missing data, we will use linear mixed models: T group as a fixed factor and unmatched or missing variables are random factors. Statistical significance is set at *p* < 0.05. Should an imbalance of twins or multiples occurs, we will perform group analyses including all singletons and one randomly selected twin or multiple from each set [58].

We will perform post hoc univariate and/or non-parametric analyses to determine if neural and clinical outcomes are associated with variations in the dose (i.e., number of hours of maternal speech delivered) or length (i.e., number of nights of delivery) of treatment, controlling for GA and PMA. Post hoc covariance analyses will permit further interpretation of either significant or non-significant treatment effects for short- and long-term neural and language outcomes. We will use multiple regression analyses to predict language outcomes from short-term neural and clinical outcomes, while controlling for group status and measures of language exposure.

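### PMA at randomisation, known before treatment and largely setting the attainable exposure, enters neither the allocation nor any T versus C comparison; adjusting for it with GA and SES would be a cheap gain

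*Protocol article*

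**What the plan says.** **Entry and exposure.** Families are approached when the infant is close to leaving the NICU for the Packard Intermediate Care Nursery (PICN) (Protocol article, Enrollment procedures). Under Study design, "The duration of the intervention will begin once an infant gets transferred to the intermediate care nursery, indicating medical stability". Under Delivery of intervention, "The intervention will occur for a minimum of 2 weeks (28 h) and a maximum of 9 weeks (126 h"), with treatment length counted from the start of the PICN stay to the MRI at 36–38 weeks PMA.

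**Allocation.** Minimisation has two factors. The first is GA at birth in two four-week bands: "Randomization will be stratified for (1) GA (24-0/7 to 27-6/7 weeks or 28-0/7 to 31-6/7 weeks), to control for potential development differences". The second is SES above or below average.

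**Control variables.** The time-related entries are "2) PMA at MRI scan; (3) the number of nights of exposure to study treatment". The list also holds GA, birth weight, antenatal steroids, infection, days of intubation and oxygen, and chronic lung changes on X-ray. PMA at randomisation is not there.

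**Analysis.** Under Analytic strategy, tests are run "to assess the statistical balance between T and C groups on the basis of GA, sex, SES, clinical complications associated with premature birth", and on language exposure. Then: "If groups are matched on all variables, we will use independent t-tests (two-tailed) to compare T versus C groups". Otherwise the unmatched or missing variables enter a linear mixed model. GA and an unspecified PMA are controlled for only in the post hoc dose and length analyses.

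**The concern.** Infants are not randomised at birth. Two infants in the same GA band can be randomised many weeks apart in PMA. The later one has often had the slower medical course and has fewer nights left before the scan. PMA at randomisation therefore carries information on prognosis and on attainable exposure. It is fixed before treatment, so adjusting for it cannot remove any of the treatment effect. Nights of exposure and PMA at MRI, the timing variables that are listed, are both observed after randomisation.

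Because PMA at randomisation is on no list, even a large difference between the arms would not trigger the adjusted model. If late-stabilising infants fell mainly in C by chance, the observed language and mean diffusivity (MD) effects would look too favourable. If they fell mainly in T, the effects would be masked and the average treatment received would be shorter. With about 21 infants per arm, such a split is not rare. The matched-groups branch also leaves GA and SES out of the comparison, although the design balances on both because they are expected to matter.

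**Working it through.** **Inputs from the protocol.** Two-sided alpha: "The significance level is *p* < 0.05 for all analyses". Effect size: "to detect an effect size at that level (Cohen’s *d* = 1.0"), with 0.9 as fallback. 21 infants per arm. Treatment 2–9 weeks, MRI at 36–38 weeks PMA.

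**Assumed.** The correlation r between PMA at randomisation and outcome is not given; I take 0 to 0.4. Infants are treated as independent. Multiples share an arm under the protocol, which would make chance imbalance somewhat larger.

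**1. The plan's own figures.** Two-sample t-test, noncentral t. With 21 per arm and d = 1.0, the noncentrality is 1/√(2/21) = 3.240 on 40 df, and power is 0.885 (stated 0.88). At d = 0.9 it is 2.916, and power is 0.812 (stated above 0.8). Power 0.8 at d = 1.0 needs 16.7, so 17 per arm (stated 17; power 0.807). All reproduce.

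**2. Spread of entry.** Earliest: 36 − 9 = 27 weeks PMA. Latest: 38 − 2 = 36 weeks PMA.

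**3. Chance imbalance.** For a covariate unrelated to the minimisation factors, the SE of the T−C difference in means is √(2/21) = 0.309 SD, with a 95% range of ±1.96 × 0.309 = ±0.60 SD.
- P(difference > 0.3 SD): 0.3/0.309 = 0.97, two-sided probability 0.33.
- P(difference > 0.5 SD): 0.5/0.309 = 1.62, two-sided probability 0.105.

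Entry cannot precede birth, so PMA at entry is tied to GA and minimising on GA removes a little of this. As a check, I assumed GA uniform over 24–32 weeks, length uniform over 2–9 weeks and entry at least half a week after birth, with minimisation at assignment probability 0.8. The SD of the difference is then just under 0.6 weeks, and it exceeds one week in 8–9% of trials. Under these assumptions one week is about 0.5 SD.

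**4. Effect of a given imbalance.** A difference of 0.5 SD shifts the unadjusted contrast by 0.5 × r outcome SD: 0.10 for r = 0.2 and 0.20 for r = 0.4.

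**5. Precision with the covariate.** The variance ratio, adjusted to unadjusted, is (1 − r²)(1 + 1/38). Power uses d/√[(1 − r²)(2/21)(1 + 1/38)] on 39 df.

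| r | variance ratio | power, d = 1.0 | power, d = 0.9 |
|---|---|---|---|
| unadjusted | 1 | 0.885 | 0.812 |
| 0 | 1.026 | 0.877 | 0.802 |
| 0.1 | 1.016 | 0.880 | 0.805 |
| 0.2 | 0.985 | 0.889 | 0.817 |
| 0.3 | 0.934 | 0.905 | 0.837 |
| 0.4 | 0.862 | 0.925 | 0.865 |

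Break-even: (1 − r²)(39/38) = 1, so r² = 1/39 and |r| = 0.16.

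**6. All three covariates, pessimistic case.** Suppose GA and SES explained nothing and were not balanced by design. The inflation becomes 1 + 3/36 = 1.083 on 37 df, and power for r = 0.2–0.4 is 0.872–0.911 at d = 1.0 and 0.795–0.845 at d = 0.9. The protocol chose both factors as prognostic and minimises on them, so the actual cost should be smaller.

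**The case against.** The best defence is that nothing here is an error. The protocol gives a reason for each minimisation factor, and two factors for 42 infants is reasonable. Imbalance in anything else is random. A reader might infer that the T versus C contrast is biased or that false positives are inflated. The documents do not support that: over repeated randomisation the unadjusted contrast is unbiased and its type I error is not raised. This stands, and limits the point to conditional error and precision.

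A reader might also take PMA at randomisation to be the only pre-treatment marker of illness course. It is not. Birth weight, infection, intubation and oxygen days and lung changes are all to be collected, and clinical complications are in the balance check. Much of this should precede randomisation, although oxygen days may continue after it. What PMA at randomisation adds beyond these is unknown. It also depends on when consent and the maternal recording were completed, and no passage says that it predicts language or MD.

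PMA at PICN entry could be recovered from PMA at MRI and nights, if nights were counted by dates in both arms. The protocol calls the variable exposure to study treatment, which is unclear for controls, and neither variable is in the balance list. This answers little.

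Finally, one might want PMA added to the minimisation. Recruitment began in November 2019, so that would change the allocation mid-trial and loosen balance on GA and SES. It is a debatable trade-off, and the point does not need it.

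**Conclusion.** The point holds as an inexpensive improvement. PMA at randomisation is known before treatment, varies widely and largely determines attainable nights (largely, because the scan date also varies). It is absent from the minimisation, the control variables and the balance list, and the matched-groups t-test also ignores GA and SES.

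The size is small to moderate. There is about a 10% chance, or slightly less, of an imbalance above 0.5 SD, which would move the contrast by 0.10–0.20 outcome SD. Adjustment for this one covariate would gain between 0.004 and 0.040 in power at d = 1.0, and between 0.005 and 0.053 at d = 0.9. These figures rest on an assumed r of 0.2–0.4, on 21 independent infants per arm and on one added covariate. Below |r| of about 0.16 there is a slight loss, at most about 0.01 in power. The planned sample size is not called into question.

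**What to change.** In Analytic strategy, replace the test-then-adjust rule for the T versus C comparisons of the 18-month CDI scores and of MD. Use a pre-specified linear model with group, GA, SES and PMA at randomisation as fixed effects, fitted whatever the balance tests show. Define PMA at randomisation as GA at birth plus postnatal age on the day of randomisation, and add it to Control variables and covariates as a pre-treatment variable. The balance tests can stay as description.

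The change needs no new data, since GA at birth and the date of randomisation give the covariate, and it alters neither the allocation nor the treatment. It costs one degree of freedom per covariate (40 to 37 in all, critical t 2.021 to 2.026) and a slight loss of precision if PMA at randomisation proves not to be prognostic. It should be fixed before anyone sees outcomes by arm.

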#### Delivery of intervention

The intervention will occur for a minimum of 2 weeks (28 h) and a maximum of 9 weeks (126 h) prior to the date of the clinical brain imaging scan. Neonates randomized to the T group (maternal speech group) will listen, via an iPod placed in cribs and/or incubators, to recordings of their mother’s speech at hourly intervals between 10:00 p.m. and 6:00 a.m. Administration of the intervention during periods when parents are unlikely to visit the hospital is expected to minimize parental knowledge for the group assignment. Recordings will be played automatically using the alarm function to avoid reliance on clinical staff. Research staff will regularly check on the status of the device to ensure proper functioning. Neonates will hear a total of 2.67 h of speech recordings per night (20 min/h × 8 h). Treatment length will be defined as the number of nights from the start of treatment (i.e., beginning of PICN stay) to the end of treatment (i.e., date of MRI scan at 36–38 weeks PMA). Within a given hour, two 10-min segments will be randomly presented to avoid synchronization with biological and sleep rhythms. Sound intensity for speech recordings is balanced between open cribs versus incubators and is below hourly NICU safety levels less than 50 dB [45].

Neonates in the C group will receive standard care. All infants in the NICU receive developmental care support from health care providers and families, and clinical staff tracks which activities are experienced by all infants through nursing documentation. Clinical staff uses a standard care path to guide which types of activities are appropriate for an infant depending on the maturity and health status. Families are generally encouraged to talk, read, and sing to their infants when visiting, if the infant is deemed in the appropriate stage. Auditory setup will be the same for neonates in the C group; however, these neonates will not hear speech recordings. This procedure ensures that parents remain blinded to the group randomization.

#### Participant retention plan

To maintain contact in preparation for longitudinal assessments of language and brain development outcomes, we plan to contact the primary caregiver of the infant participant at 6 months AA in concert with routine 6-month AA high-risk infant follow-up clinic visitation or via phone call, text message, or email for infants who are not followed in the clinical program. We will make sure that the contact information is up to date and to inform families of study procedures that will be performed for follow-up visits.

### Outcome assessment methods

The primary outcome is language development (domain) assessed through the MacArthur-Bates CDI (measure) at (metric) 18 months AA (time point), quantified as expressive and receptive language raw scores and aggregated as group means (aggregation). The secondary outcome is white matter development (domain) assessed through dMRI scans (measure) collected at (metric) two different time points (time point): (1) prior to hospital discharge (neonatal time point) and (2) at 12 months AA (1-year time point), quantified with the dMRI metric (MD) and aggregated as group means (aggregation).

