**Methods:**

This randomized controlled trial assesses the long-term effects of increased maternal speech exposure on structural connectivity at 12 months of age (age adjusted for prematurity (AA)) and language outcomes between 12 and 18 months of age AA. Study participants (*N* = 42) will include infants born very preterm (24–31 weeks 6/7 days GA). Newborns are randomly assigned to the treatment (*n* = 21) or standard medical care (*n* = 21) group. Treatment consists of increased maternal speech exposure, accomplished by playing audio recordings of each baby’s own mother reading a children’s book via an iPod placed in their crib/incubator. Infants in the control group have the identical iPod setup but are not played recordings. The primary outcome will be measures of expressive and receptive language skills, obtained from a parent questionnaire collected at 12–18 months AA. The secondary outcome will be measures of white matter development, including the mean diffusivity and fractional anisotropy derived from diffusion magnetic resonance imaging scans performed at around 36 weeks postmenstrual age during the infants’ routine brain imaging session before hospital discharge and 12 months AA.

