Our aim is to establish whether a language intervention (treatment) administered in the NICU has the potential to promote healthy language and brain development in very preterm infants. To achieve this goal, we have designed an interventional randomized controlled trial (RCT) that will test the causal effect of increased exposure to maternal speech in the NICU on language outcomes and white matter development in infants born very preterm. Our first aim will assess the long-term effects of increased maternal speech exposure on an infant’s expressive and receptive language abilities measured at 12–18 months of age adjusted for prematurity (AA). We focus on these language abilities because they have been linked to language processing abilities that are known to be strong predictors of later academic outcomes [34–36]. We hypothesize that, compared to controls, infants in the treatment group will demonstrate more advanced language skills at 12–18 months AA. Our second aim will assess the effects of increased maternal speech exposure on an infant’s white matter development at ~ 36 weeks PMA and 12 months AA. Measuring white matter development at these two ages will allow us to assess whether possible immediate effects of increased maternal speech exposure on white matter development are sustained over the first year of life. We hypothesize that, compared to controls, infants in the treatment group will demonstrate changes in dMRI measures reflecting increased white matter development. Specifically, infants in the treatment group will demonstrate lower MD.

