### Primary outcome: language development

#### MacArthur-Bates CDI

In order to measure language development and production, parents of infant participants will complete the CDI: Words and Gestures Questionnaire [46] at 12 months AA and 18 months AA via web form or mail form with guidance from a trained clinical research assistant. The CDI Words and Gestures Questionnaire is a parent checklist that evaluates both verbal and non-verbal communication, as well as some aspects of play. Split into two parts, “The Early Words” section examines infants’ intentional linguistic communication, understanding, vocabulary, and language-based social interactions, while the “Actions and Gestures” section gauges communicative gestures, play, and symbolic understanding. As these metrics of language development are related to measures of processing speed and predictive of later language outcomes, the CDI Words and Gestures Questionnaire will serve as our primary measure of language development.

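### Age at completion of the 18-month CDI is left out of the unadjusted primary comparison of raw scores, which costs precision but does not bias the test

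*Protocol article*

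**What the plan says.** All references are to the protocol article.

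- **Time point.** Outcome assessment methods has language development "assessed through the MacArthur-Bates CDI (measure) at (metric) 18 months AA (time point". Study design agrees: "At 18 months AA, parents will complete another CDI: Words and Gestures Questionnaire, the primary outcome assessment of language development".
- **Scale.** The scores are "quantified as expressive and receptive language raw scores and aggregated as group means (aggregation", so they are not age-normed.
- **Collection.** The MacArthur-Bates CDI section has parents complete the form "at 12 months AA and 18 months AA via web form or mail form with guidance from a trained clinical research assistant". No completion window is given.
- **Control variables.** The list under Control variables and covariates includes "2) PMA at MRI scan". It has no entry for age at CDI completion.
- **Analysis.** Analytic strategy checks balance on gestational age, sex, SES, clinical complications and language exposure. If the arms match on all of these, the primary comparison is an independent two-tailed t-test. If they do not, or if data are missing, a linear mixed model is used, with the unmatched or missing variables entered as random factors.

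**The concern.** A raw vocabulary count in the second year of life can be expected to depend on the child's age on the day the form is filled in. No clinic visit sets that day for a web or mail form, so actual ages will spread to some degree around 18 months. The stated rules give this spread no route into the primary analysis. Completion age is not a listed control, and because it is not a checked variable it cannot trigger adjustment. The plan does list age at measurement for the imaging outcome, but not for the primary one.

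The stake is precision. Ordinary growth between an earlier and a later form goes into the residual variance. With 21 infants per arm, chance differences in mean completion age also move the estimate.

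**Working it through.** **The plan's own figures.** Inputs from Power calculations: d = 1.0, 21 per group, alpha 0.05. Two-sided testing is from Analytic strategy. Using the noncentral t distribution with 2n − 2 degrees of freedom and noncentrality d × √(n/2):

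- n = 21, d = 1.0: power 0.885 (stated 0.88)
- n = 17, d = 1.0: 0.807; n = 16: 0.781, so 17 is the minimum for 0.80, as stated
- n = 21, d = 0.9: 0.812 (stated as above 0.8)

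The stated power reproduces.

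**Assumed inputs (not in the documents).** Growth in raw score b = 0.1 to 0.3 within-age SD per month. SD of completion age s = 0.5 to 1.5 months, independent of arm.

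**Formulas.**

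- Added variance, as a fraction of within-age variance: (b × s)²
- Effective effect size: 1/√(1 + (b × s)²)
- SD of the chance arm difference in mean completion age: s × √(2/21) = 0.309 × s
- Resulting SD of the shift in the contrast: b × s × 0.309

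| b (SD/month) | s (months) | Added variance | Effective d | Unadjusted power | SD of chance shift (SD units) |
|---|---|---|---|---|---|
| 0.1 | 0.5 | 0.0025 | 0.999 | 0.884 | 0.015 |
| 0.1 | 1.5 | 0.0225 | 0.989 | 0.878 | 0.046 |
| 0.2 | 1.0 | 0.0400 | 0.981 | 0.873 | 0.062 |
| 0.3 | 0.5 | 0.0225 | 0.989 | 0.878 | 0.046 |
| 0.3 | 1.0 | 0.0900 | 0.958 | 0.857 | 0.093 |
| 0.3 | 1.5 | 0.2025 | 0.912 | 0.822 | 0.139 |

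The last column is not an extra effect on top of the added variance. It is the same noise seen in the treatment estimate, and the t-test's standard error already contains it.

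**Validity.** With completion age independent of arm and b = 0.2, 50,000 simulated trials gave a type I error of 0.050 at s = 0.5 and 0.049 at s = 1.73 months. The unadjusted test keeps its level.

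**What adjustment returns.** Removing the age component restores d = 1.0 with 39 instead of 40 degrees of freedom, for a power of 0.885 if mean completion age happens to be equal in the arms. Averaged over chance imbalance in age, the variance of an adjusted difference is larger by a factor of about 1 + 1/(40 − 2) = 1.026. Effective d is then 1/√1.026 = 0.987 and power about 0.877. On average, therefore, adjustment gains power once (b × s)² exceeds about 0.026, and below that it costs less than 0.01.

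**The case against.** The strongest reply is that nothing stated is an error. The nominal age is fixed at 18 months and already corrected for prematurity. Raw scores at one common age are a legitimate endpoint. A research assistant guides completion, which should limit drift. A return window is the kind of detail an article may leave to the full protocol. PMA at MRI also has a particular reason to be recorded, because the neonatal scan falls in a stated range of 36 to 38 weeks and its date ends treatment. All of this stands: the absence of a window is no finding here, and the contrast with MRI is suggestive, not a contradiction.

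The reply does not reach the analysis itself. The article commits to a scale, a control list, a balance list and an unadjusted default test. A window would narrow the spread in completion age, but would leave those commitments as they are.

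Two stronger readings are tempting and should not be drawn:

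- **That age at the primary assessment is not fixed at all.** The abstract ("obtained from a parent questionnaire collected at 12–18 months AA") and the hypothesis ("infants in the treatment group will demonstrate more advanced language skills at 12–18 months AA") give a range, but Outcome assessment methods and Study design both fix 18 months. That difference in wording is a separate matter, and the present point remains once 18 months is settled.
- **That the treatment contrast is biased.** A systematic one-month gap between arms would shift it by 0.1 to 0.3 SD and raise type I error to between 0.062 and 0.158. The design offers no mechanism for such a gap: allocation is by minimization, families and research and clinical staff are blinded, and data are collected and analysed without knowledge of assignment. It would need return timing, or loss of forms, to differ by arm.

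**Conclusion.** The point holds as a cheap improvement in precision. It is not a threat to validity. Without adjustment, outcome variance rises by 0.3% to 20%, and power at d = 1.0 with 21 per arm falls from 0.885 to between 0.884 and 0.822. Even the worst corner stays above 0.80 at that effect size. The upper end needs both the steepest growth and the widest spread considered, and for much of the range the loss is small.

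These sizes rest on an assumed growth rate and an assumed spread of completion age, on that spread being independent of arm, and on all 21 forms per arm being available.

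**What to change.** Derive exact corrected age at completion of the 18-month CDI from the form date and the expected due date. Prespecify it as a fixed covariate in the primary comparison (a linear model with arm and completion age), whether or not the arms look balanced on it. It should not wait for the balance checks or enter as a random factor, because it is a continuous predictor. Keep late forms in the analysis with their actual age.

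The cost is one derived variable, one sentence in the analysis plan and one degree of freedom. If completion ages turn out to be tightly clustered, the adjustment brings no gain and loses a trivial amount of power.
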